## Statistical methods

### Statistical methods for primary and secondary outcomes

Using SPSS version 23 (SPSS Inc., Chicago, IL, USA), parametric and non-parametric statistical tests will be applied for the data analysis. Summary statistics of each group will be computed and presented as mean, standard deviation, and proportion. Using a paired *t*-test, the baseline and end of study characteristics, as well as the laboratory results of the groups, will be compared and a *P* value of <0.05 will be considered significant. Multiple regression analysis will be used to assess other factors influencing weight change. Then non-parametric Mann-Whitney *U* test will be used for asymmetrical continuous variables.

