## Objectives

### Hypothesis

Providing an ONS for 12 weeks will increase the body weight of institutionalized older adults with malnutrition or at risk of malnutrition at least by 5%.

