### Outcomes

The primary outcome measure is the percentage of intervention group participants who achieved at least 5% weight gain compared to the control group.

The secondary outcome measures include mean between-group differences of the following variables from baseline to the end of the 12th week:

I.Anthropometric measurementsBody weightHeightBody mass index (BMI)Mid-upper arm circumference (MUAC)Calf circumference (CC)Waist circumferenceTriceps skin fold thicknessII.Body compositionDXA lean body mass and fat massIII.Biochemical parametersFull Blood Count (FBC)Hs-CRP (C-reactive protein)Serum albuminTotal cholesterolSerum total 25-hydroxy vitamin DIV.Functional capacityHand grip strengthKnee extensionActivities of daily living — Barthel indexV.FrailtyFive fried model indicatorsVI.Respiratory muscle strength (peak expiratory flow rate)VII.Energy and macronutrient intake per dayVIII.Cognitive status (Montreal Cognitive Assessment)IX.Physical activity levelPhysical Activity Scale for the Elderly (PASE)International Physical Activity Questionnaire (IPAQ – short form)

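### The main stated test is a within-group paired t-test, and no stated procedure compares the arms on the primary responder percentage or on symmetric continuous secondary outcomes

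*Protocol article*

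**What the plan says.** Under Outcomes, the protocol article defines the primary outcome against control: "The primary outcome measure is the percentage of intervention group participants who achieved at least 5% weight gain compared to the control group". The secondary outcomes are comparative too: "The secondary outcome measures include mean between-group differences of the following variables from baseline to the end of the 12th week". The Sample size section plans for two independent proportions, 0.30 in control and 0.75 in the intervention group, with two-sided alpha 5%, beta 10% and 20% drop-out, giving 25 per arm.

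The section on statistical methods for primary and secondary outcomes opens with a general remark that parametric and non-parametric tests will be used. It then says:

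- for proportions, description only: "Summary statistics of each group will be computed and presented as mean, standard deviation, and proportion";
- for change over the study, with P<0.05 as the threshold: "Using a paired *t*-test, the baseline and end of study characteristics, as well as the laboratory results of the groups, will be compared";
- for weight change: "Multiple regression analysis will be used to assess other factors influencing weight change";
- for skewed variables: "Then non-parametric Mann-Whitney *U* test will be used for asymmetrical continuous variables".

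The Hypothesis section does not mention the control group: "Providing an ONS for 12 weeks will increase the body weight of institutionalized older adults", by at least 5%.

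**The concern.** A paired t-test compares each participant with his or her own baseline. It cannot compare two independent arms, and it does not apply to a responder percentage, which has no baseline value. The outcomes and the sample size call for a between-arm contrast, while the main test named gives within-arm inference.

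The plan itself expects gains without the supplement. It assumes that 30% of controls will gain at least 5%, and both arms receive dietary advice (Intervention description). A significant before-and-after change in the supplement arm is therefore weak evidence of a supplement effect, and a hypothesis that omits control invites that reading. Leaving the primary test unnamed also means it could be chosen after the data are seen.

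**Working it through.** **1. What the trial was sized for.** Inputs from Sample size: pA = 0.30, pB = 0.75, critical value 1.96, beta 0.10 (normal value 1.2816), drop-out 20%. The standard two-proportion formula is

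n = [pA(1−pA) + pB(1−pB)] × [(1.96 + 1.2816)/(pA − pB)]²
= (0.21 + 0.1875) × (3.2416/0.45)² = 20.63 per arm.

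Multiplied by 1.2 this is 24.75, so 25 per arm and 50 in total, as stated. (Dividing by 0.8 gives 25.8, so 26. The formula as printed has a plus sign and omits pB(1−pB); taken literally it gives about 52 per arm, so it looks like a typesetting slip.) The trial is therefore sized for a between-arm test of proportions.

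**2. Which stated procedure could deliver that comparison.**

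| Procedure named | Compares arms? | Covers the responder percentage? |
|---|---|---|
| Summary statistics, including proportions | Description only | No test |
| Paired t-test, P<0.05 | No, within participant | No |
| Multiple regression on weight change | Arm not named as a term | No, outcome is weight change |
| Mann-Whitney U | Yes | No, skewed continuous variables only |

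No row tests the primary outcome, and none compares the arms on a symmetric continuous secondary outcome.

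**3. What the paired test does when there is no supplement effect.** Let 30% respond in both arms, the protocol's own control figure. Assume percent weight change is normal with standard deviation SD, and treat the paired test as a one-sample t-test of mean percent change. The article gives no SD, so 3 to 6 points is an assumed range.

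- The mean gain that puts 30% at or above 5% is 5 − 0.5244 × SD.
- The noncentrality with n = 25 is √25 × mean/SD. The power is the upper tail of a noncentral t with 24 degrees of freedom beyond the two-sided 5% critical value.

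| Assumed SD (points) | Mean gain (%) | Mean/SD | Significant in supplement arm, n=25 | Same, n=20 |
|---|---|---|---|---|
| 3 | 3.43 | 1.14 | 99.98% | 99.8% |
| 4 | 2.90 | 0.73 | 93.6% | 86.8% |
| 5 | 2.38 | 0.48 | 62.6% | 52.4% |
| 6 | 1.85 | 0.31 | 31.7% | 25.9% |

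A between-arm test at the 5% level rejects in about 5% of such trials nominally.

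**4. A different rate: significant in the supplement arm but not in control.** With the same true change in both arms this is p(1−p), where p is the n=25 column: 0.02%, 6%, 23% and 22% for SDs of 3, 4, 5 and 6.

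**The case against.** The strongest reply is that the article is silent on the primary test, not contradictory. The paired test is attached to baseline and end-of-study characteristics and laboratory results, not expressly to the responder percentage. A condensed article may leave the test for a clearly defined two-arm proportion to a fuller document. The comparative intent is plain from the Outcomes and Sample size sections. Mann-Whitney U is a between-group test, the phrase about other factors may imply that arm is in the regression, and the Discussion plans comparison within and between groups for bone density.

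Part of this stands. A reader might infer that the trial discards its control group, that the paired test is the designated test of the primary outcome, or that the primary comparison will never be tested. The documents do not support these readings: they show only that no stated procedure makes the comparison. Nor do they say that the hypothesis would be judged in the supplement arm alone.

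A reader might also take the rate of significance in the supplement arm but not in control as the trial's false-claim rate. The article states no such decision rule. Under the protocol's own 30%, that rate runs only from about 0% to 23%, depending on the assumed SD.

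The silence argument does not clear the section. It is headed as the methods for the primary and secondary outcomes, and it does state methods. For the continuous secondary outcomes the mismatch is direct: between-group mean differences are the outcome, and a within-group test is the main method. The between-group statement in the Discussion covers bone density only.

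**Conclusion.** The concern holds in this form: the main stated test is within-group, and no stated procedure compares the arms on the primary responder percentage or on symmetric continuous secondary outcomes, although both are defined as between-group comparisons and the trial is sized for two proportions.

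Followed as written, a shared gain could be significant in the supplement arm without any supplement effect, in about 32% to nearly 100% of trials with 25 per arm. This rests on 30% responders in both arms, normally distributed percent change, and assumed SDs of 6 down to 3 points. It illustrates continuous weight change; it is not an error rate for the responder outcome. Reading such a result as a supplement effect is a risk, not a certainty, since the control arm's own paired result could show the same gain. The mismatch itself does not depend on the simulated range. Because it concerns the primary inference, it should be corrected before the data are analysed.

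**What to change.** In the statistical methods section:

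- **Primary analysis.** State the between-arm difference in the proportion with at least 5% weight gain at week 12, by allocated arm, with a 95% confidence interval and one prespecified two-sided test of two proportions. Naming a single test matters: at 0.30 against 0.75, power is 91.5% (z test) or 88.1% (Fisher exact) with 25 per arm, and 84.1% or 73.1% with 20 per arm after the planned drop-out.
- **Continuous secondary outcomes.** Compare the arms at week 12 by ANCOVA adjusted for the baseline value.
- **Paired tests.** Keep them as description only, with no claim of treatment effect resting on them.

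In the Hypothesis section, reword the statement as a comparison: a higher proportion gains at least 5% with the supplement than with control.

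The cost is wording and minor analysis work. No new data, visits or participants are needed.

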## Trial design

This study is a randomized-controlled, parallel-group, clinical trial that will include an intervention group (200 mL of high-energy and protein oral nutrition supplement daily before bed for 12 weeks) and a control group of older adults aged above 60 years who are malnourished or at risk of malnutrition. Participants satisfying the eligibility criteria will be allocated to control and intervention groups equally (1:1). The intervention length is 12 weeks. The CONSORT flow diagram of the trial is provided in Fig. 1. Items included in this protocol conforms to standards described in the SPIRIT (Standard Protocol Items: Recommendations for Interventional Trials) Checklist (Additional File 1).

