### Sample size

The sample size calculation was based on studies indicating that a weight gain of 5% can be expected with an ONS intervention, and is sufficient to achieve an overall improvement in nutritional status [23]. A clinically relevant difference was defined as an increase in this fraction to 75% or greater in the treatment arm. Hence, a total of 50 adults will be recruited for the study (alpha, 5%; beta, 10%; drop-out rate, 20%) after the screening for eligibility against inclusion/exclusion criteria. Then, participants will be randomly assigned into two groups (*n*=25 intervention and *n*=25 control). The formula used for sample size calculation was as follows:$${n}_{B} =\left( \frac{{p}_{A \left( 1- {p}_{A}\right)}}{k} \right)+{\left(\frac{z1- \frac{\propto }{2 } + z1- \beta }{{p}_{A-{P}_{B}}}\right)}^{2}$$$${n}_{B}$$ = Sample size in one arm

*P*_*A*_ = Proportion of participants expected to achieve 5% improvement in body weight in the control group (0.3) [23]

*P*_*B*_ = Proportion of participants expected to achieve 5% improvement in body weight in the intervention group (0.75) [23]

*Κ* = Sampling ratio (1:1)

*Z*_*α*_ = Critical value of the normal distribution at *α* (*α* is 0.05 and the critical value is 1.96)

*Z*_*β*_ =Critical value of the normal distribution at *β* (*β* is 0.1)

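### The secondary outcomes are defined as between-group differences in change, but the only parametric test named for them is a paired, within-arm t-test

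*Protocol article*

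**What the plan says.** **Outcomes.** The secondary outcome measures, with body weight at the head of the list, are "mean between-group differences of the following variables from baseline to the end of the 12th week". That is a contrast between arms in change over 12 weeks.

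**Statistical methods for primary and secondary outcomes.** Three methods bear on continuous data:
- a paired t-test comparing baseline with end of study, laboratory results included, at P < 0.05;
- a Mann-Whitney U "test will be used for asymmetrical continuous variables", with no statement whether it is applied to week-12 values or to changes;
- a regression: "Multiple regression analysis will be used to assess other factors influencing weight change". Its terms are not listed.

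No two-sample parametric test and no between-arm model is named.

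**Participant timeline and Table 2.** Nearly all listed secondary outcomes are scheduled at baseline and at week 12. Height is an exception, with a baseline measurement only. Weight, several other anthropometric measures, grip strength, knee extension and dietary intake are also taken at week 4.

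**The concern.** A paired t-test of baseline against week 12 asks whether one arm changed. It does not ask whether the arms changed by different amounts, which is what the Outcomes section promises. For a roughly symmetric continuous variable, an analyst who follows the text would produce two within-arm P values and no estimate of the treatment effect.

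The usual next step is to read significance in one arm and its absence in the other as evidence of an effect. That inference is unsound, and this trial is exposed to it. Both arms receive dietary advice before baseline, and the sample size section itself expects a proportion of 0.3 of control participants to reach a 5% weight gain. Some change in both arms is therefore expected. The arms are small, and the list of secondary outcomes is long.

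**Working it through.** **1. The plan's own figure.** The methods text gives no figure for the secondary outcomes, so the only one to reproduce is the sample size. Inputs from the Sample size section: control proportion 0.30, intervention proportion 0.75, two-sided 5% (z = 1.96), power 90% (z = 1.2816), drop-out 20%. With the usual unpooled two-proportion formula:

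n = [0.30 × 0.70 + 0.75 × 0.25] × [(1.96 + 1.2816) / 0.45]² = 0.3975 × 51.89 = 20.63 per arm.

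20.63 × 1.2 = 24.75, so 25 per arm and 50 in total, as stated. This figure rests on the binary primary outcome and is not affected by the present point. After 20% drop-out, 25 × 0.8 = 20 completers per arm, the number used below.

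**2. What each named method delivers.**

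| Method named | Compares arms? | Estimates a mean difference in change between arms? |
|---|---|---|
| Paired t-test | No | No |
| Mann-Whitney U (skewed variables only) | Yes | No |
| Multiple regression (weight change only) | Not stated | Not stated |

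The promised contrast is not delivered for symmetric continuous outcomes. For weight it is left uncertain.

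**3. Error from reading two within-arm tests.** Let δ be the true mean change in units of the SD of change, the same in both arms, so that there is no treatment effect. The documents give no value, so δ is an assumption. Let π be the power of a two-sided 5% paired t-test with 20 participants (noncentral t, 19 degrees of freedom, noncentrality δ√20). The arms are independent, so

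P(supplement arm significant, control arm not) = π(1 − π).

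| δ (assumed) | π | π(1 − π) |
|---|---|---|
| 0 | 0.050 | 0.048 |
| 0.3 | 0.247 | 0.186 |
| 0.4 | 0.397 | 0.239 |
| 0.5 | 0.564 | 0.246 |
| 0.8 | 0.924 | 0.070 |

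A simulation of 40,000 trials gave 0.187 at δ = 0.3 and 0.243 at δ = 0.5, in agreement. The quantity cannot exceed 0.25, reached at π = 0.5, and it falls again when both arms change strongly. For comparison, a direct two-sided 5% test between arms would wrongly favour the supplement in 2.5% of trials.

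**4. What baseline adjustment adds to a between-arm comparison.** Let r be the correlation between baseline and week-12 values, with equal SDs at the two times. The documents give neither r nor an SD, so both are assumptions. Relative to a comparison of week-12 values alone, the variance of the estimated difference is 2(1 − r) for change scores and 1 − r² for the baseline-adjusted model. Adjusted against change score:

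(1 − r²) / [2(1 − r)] = (1 + r) / 2.

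| r (assumed) | (1 + r)/2 | Variance saved | Power, change score | Power, adjusted |
|---|---|---|---|---|
| 0.5 | 0.75 | 25% | 0.35 | 0.45 |
| 0.7 | 0.85 | 15% | 0.53 | 0.60 |
| 0.9 | 0.95 | 5% | 0.94 | 0.95 |

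Power is for an assumed difference of 0.5 SD of the week-12 value with 20 per arm. Body weight over 12 weeks is likely to sit near the last row, and noisier measures higher up.

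**The case against.** The strongest reply is that the choice of model and covariates is commonly left to an analysis plan, and that a condensed article need not mention analysis of covariance. That is right, and the absence of that model alone would be a weak point. It does not answer the mismatch: the article names a test, and the test does not fit the outcome that the article defines.

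It may also be said that the paired t-test sentence refers to the groups and was meant as a comparison between them. If so, the test is misnamed, because participants are not matched across arms. The text needs correcting on either reading.

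A reader might infer several stronger charges. The documents do not support them:
- *Baseline data are thrown away.* They are not. A paired test uses every participant's baseline value; its fault is that it stays within an arm.
- *The Mann-Whitney test ignores baseline.* The text does not say whether it is run on final values or on changes, and the wording of the outcomes makes changes a fair reading.
- *The regression excludes the treatment effect.* Factors described as other may well be factors besides the supplement, with arm in the model. The text neither commits to this nor rules it out.
- *Continuous weight is lost.* It is a listed secondary outcome. That a continuous comparison can be more powerful than a 5% cut is an argument about the binary primary outcome, not about adjustment for baseline.
- *Adjustment brings a large gain in precision.* That holds for a high r against a comparison of week-12 values alone, which the plan does not specify. Against changes, the gain for weight is probably small.

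A plain between-arm comparison of changes would also cure the mismatch. Baseline adjustment is preferable but is not the only remedy.

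**Conclusion.** The point holds as an inconsistency between the defined secondary outcomes and the test named for them. Followed as written, the plan would not estimate the between-arm difference in change for symmetric continuous outcomes. The cost is a chance of about 19% to 25% per outcome of a misleading pattern favouring the supplement when both arms change equally. This assumes a common change of 0.3 to 0.5 SD, 20 completers per arm, and that the effect is read from the two within-arm tests. The chance is lower outside that range of change. The saving from baseline adjustment over change scores is secondary: 5% to 25% of variance for r from 0.9 down to 0.5, all assumed. The text should be corrected before analysis. The primary outcome and the sample size of 50 are not affected.

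**What to change.** For each continuous secondary outcome measured at both baseline and week 12, state that the inferential analysis is a between-arm linear model of the week-12 value on arm and baseline value, reporting the adjusted difference with its 95% CI. For skewed variables, fit the model on a transformed scale or give a bootstrap interval. Keep within-arm paired tests as descriptive only, and say that no treatment effect will be inferred from them. If the regression of weight change is retained, list its terms and separate it from the treatment comparison. Height falls outside this rule because no week-12 measurement is scheduled.

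Adjusting for sex and using the week-4 values in a mixed model are optional.

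The cost is a few sentences in the statistical methods or the analysis plan. The models are available in SPSS, and no new data, participants or change to the primary outcome are needed.

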### Interim analysis

The data safety monitoring committee and investigators will consider and decide to terminate the trial, if serious adverse events related to the intervention. Thereafter, an interim analysis will be conducted from the available data. The Sri Lanka Clinical Trial Registry and Ethics Review Committee will have access to interim results.

### Methods for additional analysis (e.g., subgroup analysis)

Subgroup analysis of the primary and secondary outcomes will be performed according to gender.

### Methods in analysis to handle protocol non-adherence and any statistical methods to handle missing data

Each participant’s consumption of the ONS will be monitored on a weekly basis to assess adherence to the intervention. If a participant is unable to consume the supplement continuously for more than five days due to hospitalization or any other reason, they will be considered as “non-adherent” to the intervention. Using Multiple imputation methods accessible in SPSS, the primary outcome data of the participants will be randomized to the intervention but non-adherent participants will be imputed [29].

We expect the proportion of missing data to be below 5% for the primary outcome. We will not perform multiple imputations for the primary outcome unless more than 5% of the data are missing. The secondary outcomes will be assessed in a full analysis set.

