### Intervention description

Before the baseline data collection, both the treatment and control groups will be given dietary advice, during which they will be educated on the importance of including each food group, developing healthy habits, avoiding alcohol and smoking, and maintaining a healthy level of physical activity. Subsequently, they will be randomized to treatment and control groups. During the 12-week study period, participants randomized to the ONS treatment group will receive a 200mL serving of an oral nutrition supplement (prepared by adding 4 level scoops of Entrasol Platinum, Kalbe (Pvt). Ltd (57g) into 200 mL of lukewarm water) daily before bed which contains 12 g protein and 247 kcal per serving, in addition to their usual diet for 12 weeks. The nutritional composition of the ONS is summarized in Table 1.

**Table 1 Tab1:** Nutritional composition (serving size: 4 scoops [57 g] of ONS)

		**% DV**	**Per serving**	**Per 100 g**
**Total calories**	kcal		247	434
**Total fat**	g	12	8	14
*SFA*	g	23	4.5	8
*MUFA*	g		2	3
*PUFA*	g		1	2
*Trans fatty acids*	g		< 0.5	< 0.5
*Cholesterol*	mg		< 0.5	< 0.5
**Protein**	g	20	12	21
**Total carbohydrate**	g	10	32	55
*Dietary fiber*	g	17	5	9
*Sucrose*	g		7	12.5
*Sodium*	mg	10	153	268
*Potassium*	mg	2.5	126	221
*Vitamin A*	mcg	30	184	323
*Vitamin B*_*1*_	mg	25	0.3	0.55
*Vitamin B*_*2*_	mg	25	0.4	0.71
*Vitamin B*_*3*_	mg	30	4.7	8.2
*Vitamin B*_*5*_	mg	40	2.1	3.6
*Vitamin B*_*6*_	mg	35	0.4	0.75
*Vitamin B*_*7*_*/Biotin*	mg	60	17.6	30.7
*Folic acid*	mcg	30	125	220
*Vitamin B*_*12*_	mcg	30	0.7	1.3
*Vitamin C*	mg	40	26.8	64.5
*Vitamin D*_*3*_	mcg	20	2.8	4.9
*Vitamin E*	mg	30	4.6	8.1
*Calcium*	mg	20	219	384
*Magnesium*	mg	8	26.6	46.6
*Phosphorus*	mg	15	88.7	156
*Iron*	mg	9	2.1	2.7
*Iodine*	mcg	30	46.2	81
*Zinc*	mg	30	3.9	6.8
*Chromium*	mcg	15	3.3	5.8
*Selenium*	mcg	15	4.1	7.2

*SFA* Saturated fatty acids, *MUFA* Monounsaturated fatty acids, *PUFA* Polyunsaturated fatty acids

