### Strategies to improve adherence to intervention

After starting the intervention, online video calls (WhatsApp or Viber) will be made to caregivers of the selected elderly care institution on a daily basis. The first call will be made to remind participants to ingest either treatment (200 mL of Entrasol Platinum) or control (200 mL of water), after dinner. A second call will be made to make sure whether all participants in the intervention group have consumed the supplement and all the participants in the control group have consumed an equal quantity of water. There will be random visits from the data collection team during the administration of ONS.

Compliance with ONS intake will be calculated over 12 weeks (84 days) using the participant's intake record and return of balance product containers. The percentage of compliance will be calculated by the following formula:

The number of supplement containers consumed is divided by the number of supplement containers instructed to consume, multiplied by 100.

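### The non-adherence flag depends on one unbroken gap, ignores the trial's own compliance percentage, and selects whose primary outcome is imputed, so it can rank participants opposite to their intake

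*Protocol article*

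**What the plan says.** Three places in the protocol article bear on this.

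- **Intervention description.** The supplement is one serving, taken "daily before bed which contains 12 g protein and 247 kcal per serving", for 12 weeks.
- **Strategies to improve adherence to intervention.** Exposure is measured cumulatively: "Compliance with ONS intake will be calculated over 12 weeks (84 days"), from the intake record and returned containers. The formula is: "The number of supplement containers consumed is divided by the number of supplement containers instructed to consume, multiplied by 100". No cut-off is attached to the result.
- **The section on non-adherence and missing data.** Consumption is "monitored on a weekly basis to assess adherence to the intervention". The classification then turns on an interruption: "If a participant is unable to consume the supplement continuously for more than five days due to hospitalization or any other reason", in which case "they will be considered as “non-adherent” to the intervention". The next sentence, which is grammatically damaged, gives the consequence for the primary outcome: data of those "randomized to the intervention but non-adherent participants will be imputed". The section goes on to say that multiple imputation of the primary outcome is done only if more than 5% of the data are missing.

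**The concern.** The plan holds two descriptions of supplement intake, and they are not connected. One is a percentage over the whole period, which measures how much was taken. The other is a yes/no flag for a long interruption, which does not. The section that treats the primary outcome uses the flag and leaves the percentage aside.

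Servings missed without forming a run of six days never count, however many there are, while one six-day run counts even if nothing else was missed. The flag is then given an analytic role: it picks out intervention participants whose 12-week outcome is to be imputed. If that includes people who were weighed at week 12, a real measurement is replaced by a model draw because of a criterion that need not reflect exposure. The flag concerns the supplement, so it can act in one arm only.

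**Working it through.** **Inputs**

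- Period: 12 weeks × 7 = 84 days, which reproduces the plan's own figure under adherence strategies.
- Schedule: one serving a day, so 84 servings; 247 kcal per serving (intervention description).
- Flag: a run of more than five days, that is, six or more consecutive missed days.
- Arm size: 25, with a 20% drop-out allowance (sample size section).

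Full intake is 84 × 247 = 20,748 kcal.

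**Lowest intake that escapes the flag.** Cut the 84 days into 84/6 = 14 blocks of six consecutive days. A block with no serving would be a six-day run, so each block needs at least one serving and the minimum is 14. Five days missed and one taken, repeated 14 times, attains it. A day-by-day search over all patterns gives the same minimum.

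**Highest intake that triggers the flag.** One run of exactly six missed days: 84 − 6 = 78 servings.

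| Pattern | Servings | Share of 84 | Energy (kcal) | Flag |
|---|---|---|---|---|
| Five missed, one taken, repeated | 14 | 16.7% | 3,458 | adherent |
| Every other day | 42 | 50.0% | 10,374 | adherent |
| One six-day gap, otherwise complete | 78 | 92.9% | 19,266 | non-adherent |

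The third participant took 78 − 42 = 36 more servings than the second and gets the worse label.

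**Sensitivity to the wording**

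- If the trigger were five or more consecutive days, the same block argument gives 16 servings as the minimum (84/5 = 16.8, so 16 full blocks): 16/84 = 19.0%. The conclusion is unchanged.
- If the text meant more than five missed days in total, the 17% and 50% patterns would be flagged. The 93% pattern would be flagged too, and the lowest adherent intake would be 79/84 = 94.0%. That removes the reversed ranking but makes the rule very strict. Consecutive days is the natural reading.

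**Weight of one person in the primary outcome.** The outcome is a responder proportion. One participant is 1/25 = 4 percentage points of the intervention arm, or 1/20 = 5 points if 20 remain after the allowed drop-out (25 × 0.8 = 20). This is the most that one imputed value can move the proportion.

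**The 5% condition.** With 50 participants, two missing weights are 2/50 = 4% and three are 3/50 = 6%, so three missing weights open the way to multiple imputation. The text does not say whether flagged participants count toward that total, or whether their imputation is subject to the condition at all.

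**The case against.** The best defence is that the two measures serve different purposes: the percentage records cumulative exposure and the flag records interruption, which is not in itself a contradiction. That stands, and a reader should not infer that the flag is the plan's only measure of exposure. The difficulty is that the measure given a role in the analysis is the one that does not track intake.

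Four stronger readings are tempting, and the document does not support them.

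- **That intake near 17% is to be expected.** It is a mathematical bound. Two video calls a day, random visits, nurses assisting with the supplement and weekly review make it unlikely, and the 50% pattern would also need sustained failure of that supervision. The six-day gap is the realistic case, since the rule itself names hospitalisation.
- **That an adherent-versus-non-adherent comparison would be distorted.** No per-protocol analysis is planned in the statistical sections. The stated consequence runs through imputation.
- **That flagged participants are sicker rather than less exposed.** They have missed at least six servings and possibly many more, and the rule covers any reason.
- **That counting containers is itself an error.** The article does not give the container size, and compliance also draws on an individual intake record.

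It can also be said that the 5% condition may keep the flag from ever affecting the result, and that the damaged sentence may mean only that missing weights of non-adherent participants are imputed. Both are possible, and they limit how firmly the harm can be stated. They do not rescue the rule, because the text as it stands permits the other reading. A cut-off could be left to an analysis plan, but here the protocol fixes a rule, so this is more than an omission.

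**Conclusion.** The point holds. The flag is set by one unbroken gap of more than five days, takes no account of the compliance percentage the trial already collects, and can call 50% intake adherent (17% at the theoretical limit) and 93% intake non-adherent. Its stated use is to select intervention participants for imputation of the primary outcome, where each person is worth up to 4 percentage points of the arm's responder proportion, or 5 with 20 evaluable.

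The conclusion assumes consecutive days, one scheduled serving on each of 84 days, and that the imputation sentence reaches participants with a measured weight. The document gives no basis for estimating how many would be misclassified, so the percentages show what the rule allows, not what will happen. Severity is minor to moderate.

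**What to change.** In the section on non-adherence and missing data:

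1. Replace the gap rule with cumulative servings consumed out of 84, taken from the intake record and expressed as the compliance percentage already defined. Fix one cut-off before the analysts are unblinded, for example 80%, which is a convention.
2. Use that classification only in a supplementary adherence analysis.
3. Report gaps of more than five days descriptively, with reasons.
4. State that adherence status does not trigger imputation. Measured week-12 weights are analysed in the randomised arm whatever the intake, and only missing weights are imputed, in either arm. Rewrite the damaged sentence accordingly and make clear that the 5% condition counts missing weights only.

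In the adherence section, align the formula with servings, or state how a container converts to servings.

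The cost is small: wording in two sections, using records the trial already plans to keep. The downside is that any cut-off is conventional. Step 4 matters most, because a better cut-off alone would still leave measured weights open to being imputed.
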